### Treatment Assignment

All Patients will be assigned the same treatment regimen within this study

### Treatment Planning

For radiotherapy, patients will be immobilized using an individually manufactured head mask. For treatment planning, contrast-enhanced CT as well as MR-imaging will be performed for optimal target definition.

Organs at risk such as the brain stem, optic nerves, chiasm and spinal chord will be contoured. Dose constraints of normal tissue will be respected according to Emami et al. [21].

The carbon ion boost will consist of the GTV including the area of contrast enhancement on T1-weighted MR-imaging; the CTV_Carbon _for the boost will be defined adding a safety margin of 5 mm.

Amino-Acid-PET or ^68^Ga-Dotatoc-PET may be used in addition to contrast-enhanced MRI for target volume definition but is not mandatory.

For photon treatment, the CTV_Photon _will be defined, which is applied as 3D-conformal treatment or as high-precision photon radiotherapy such as FSRT or IMRT. The CTV_Photon _will be contured including the GTV and sub clinical microscopic tumor (e.g. including the pre-operative tumor or post-operative tumor bed, peritumoral edema, hyperostotic changes if any, and dural enhancement or thickening as seen in the CT/MRI at diagnosis) plus a 1 cm safety margin. The margin may be reduced with respect to anatomical borders or organs at risk at the discretion of the investigator. Treatment Planning for Photon Radiotherapy will be performed using the Planning Systems available at the Department of Radiation Oncology in Heidelberg, Germany (including HELAX-Masterplan/Nucletron, Virtuos-Konrad/Siemens, or STP/Stryker-Leibinger).

Carbon ion RT planning is performed using the treatment planning software PT-Planning (Siemens, Erlangen, Germany) including biologic plan optimization. Biologically effective dose distributions will be calculated using the a/ß ratio for meningioma as well as for the endpoint late toxicity to the brain.

No interruptions >4 days between the end of photon radiotherapy and the carbon ion boost are allowed.

Patient positioning prior to radiotherapy will be evaluated by comparison of x-rays to the DRRs. Set up deviations >3 mm are corrected prior to radiotherapy.

### Dose Prescription Carbon Boost

The intensity-controlled rasterscan system will be used for beam application. Six fractions of a single dose of 3 Gy E up to a total dose of 18 Gy E will be prescribed to the maximum of the calculated dose distribution for the target volume. Treatment planning aims at the coverage of the target volume by the 90%-isodose line.

Dose specification is based on biologic equivalent dose because of the high relative biologic effectiveness (RBE) of carbon ions, which differs throughout the target volume due to its dependence on various factors. RBE will be calculated at each voxel throughout the target volumes and biological optimization will be performed. The dose prescription used is related to the isoeffective dose GyE using daily fractions of 2 Gy and a weekly fractionation of 5 × 2 Gy.

### Follow-up

After completion of study treatment no further adjuvant treatment is scheduled or recommended. Any systemic treatment or chemotherapy or any other treatment applied is not part of the clinical trial.

For tumor progression, treatment alternatives will be evaluated and discussed in the interdisciplinary setting considering options of neurosurgical resection, systemic treatment such as chemotherapy, a second course of radiation therapy, or other.

This study will use the International Common Terminology Criteria for Adverse Events (CTCAE) version 4.0 for toxicity and adverse event reporting. A copy or the CTCAE can be accessed from the CTEP home page (http://ctep.cancer.gov/protocolDevelopment/electronic_applications/ctc.htm).

Safety and toxicity of the study treatment will be evaluated by clinical neurological examination as well as neuro-imaging studies (MRI or CT).

### - Progression-free Survival -

Progression-free survival is the primary endpoint of the study. Progression-free survival will be counted from the first day of radiotherapy treatment until the date of the first event of either progression or death due to any cause. Patients alive without progressive disease at the time of data analysis will be censored at the time of the most recent follow-up visit.

#### Complete remission

Remission of all contrast-enhancing lesions on CT or MRI without worsening of neurologic status

#### Partial remission

at least 50% remission of the contrast-enhancing lesions on CT oder MRI without increase in steroid medication and without worsening of the neurologic status

#### Stable disease

Remission of the solid tumor/contrast-enhancing lesion on CT or MRI of less than 50% or progression of the solid tumor/contrast-enhancing lesion on CT or MRI of less than 25%, without increase in steroid medication of worsening of the neurologic status

#### Progression

Increase in solid tumor/contrast-enhancing lesion of 25% or more or development of a new lesion

#### Progression-free survival will be assessed following the target lesion(s) as defined hereunder

The initial assessment of the disease (including CT and MRI) must be performed between neurosurgical intervention and the beginning of study treatment. Follow-up assessments (including MRI or CT) will be performed as described until disease progression (even after the end of the study).

Special attention should be given so as to avoid tissue reaction to radiation treatment to be classified as tumor or disease progression. Such variations in post-radiotherapy imaging may continue for months, and may be accompanied by clinical signs and symptoms. In addition, surgical procedures may cause increased contrast uptake which should be differentiated from tumor progression. The clinical follow-up must dictate how the initial progression of the lesion should be labeled. If the course of events shows that true progression indeed occurred, the date of the first increase is to be considered as the date of progression. The principal investigator or the study coordinator may be contacted for further discussion on a case by case basis.

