### Inclusion criteria

Patients meeting all of the following criteria will be considered for admission to the trial:

- histologically confirmed atypical meningioma

- macroscopic tumor after biopsy or subtotal resection - Simpson Grade 4 or 5

- prior photon radiotherapy to the CTV_Photon _of 48-52 Gy

- beginning of study treatment no later than 12 weeks after surgery

- age ≥ 18 years of age

- Karnofsky Performance Score ≥60

- For women with childbearing potential, adequate contraception.

- Ability of subject to understand character and individual consequences of the clinical trial

- Written informed consent (must be available before enrolment in the trial)

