### Radiological progression

The lesion must be measured in the two largest perpendicular diameters; the area should be defined as the product of these two diameters.

- Increase of the lesion on MRI or CT scans of more than 25% as measured by two perpendicular diameters compared to the smallest measurements ever recorded for the same lesion by the same technique.

- The appearance or new lesions with or without contrast enhancement.

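### The reference scan may date from any time between surgery and study treatment, and growth is judged against the smallest measurement ever, so growth before irradiation can count towards a PFS event

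*Protocol article*

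**What the plan says.** All places are in the protocol article.

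- **Baseline.** The section on assessing PFS by target lesions says the initial assessment, including CT and MRI, "must be performed between neurosurgical intervention and the beginning of study treatment". It fixes no point within that window.
- **Length of the window.** Inclusion criteria: "beginning of study treatment no later than 12 weeks after surgery".
- **Who enters.** Inclusion criteria: "macroscopic tumor after biopsy or subtotal resection - Simpson Grade 4 or 5". Every patient therefore has a measurable residue that can grow.
- **Threshold.** Radiological progression: "Increase of the lesion on MRI or CT scans of more than 25% as measured by two perpendicular diameters".
- **Reference for that threshold.** The same section has the growth judged as "compared to the smallest measurements ever recorded for the same lesion by the same technique". No earliest date is set for the reference.
- **Clock.** The PFS section: "Progression-free survival will be counted from the first day of radiotherapy treatment until the date of the first event".
- **Dating.** Once the course of events shows that progression was real, "the date of the first increase is to be considered as the date of progression".
- **Planning images.** Treatment Planning: "For treatment planning, contrast-enhanced CT as well as MR-imaging will be performed for optimal target definition". These images serve target definition and are not named as the response reference.

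**The concern.** The reference for growth can lie before the start of the PFS clock. Suppose a residue grows 30% between an early postoperative MRI and the start of radiotherapy, and then stays unchanged for 3 years. At the first follow-up MRI it is still 30% above its smallest recorded measurement, so it meets the radiological criterion although nothing grew after irradiation. Slower growth does not trigger the criterion alone, but it leaves less than 25% of room afterwards.

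At stake is what the primary endpoint measures. A 3-year PFS status that depends on how soon after surgery a patient was scanned mixes growth of untreated tumour with the effect of treatment. With 37 evaluable patients, one or two extra events matter.

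**Working it through.** **1. The plan's own figure.** Inputs from Sample Size Calculation: p0 = 0.50, p1 = 0.70, one-sided exact binomial test, n = 37, stated actual alpha 0.049. With X the number of progressions or deaths:

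- P(X ≤ 13 | 37, 0.50) = 0.0494
- P(X ≤ 13 | 37, 0.30) = 0.807, so beta = 0.193

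The stated alpha is thus reproduced by rejecting at 13 or fewer events. The article prints the rule as fewer than 13, that is 12 or fewer, which gives alpha 0.0235 and power 0.698. That mismatch is a separate matter; both versions are carried below.

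**2. What the 25% threshold means.** A 25% rise in the diameter product is √1.25 = 1.118, or 11.8% in each diameter, and 1.25^1.5 = 1.398, or 39.8% in volume.

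**3. Growth in the gap.** The article gives no growth rate, so exponential growth with volume doubling time Td is an assumption. Over a gap t the diameter product grows by the factor 2^(2t/(3Td)). Setting this to 1.25 gives Td = t × 2 ln 2 / (3 ln 1.25) = 2.07 t.

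- t = 12 weeks (the ceiling): the threshold is crossed if Td is below about 24.9 weeks.
- t = 7 weeks: below about 14.5 weeks.

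The 7-week case arises if study treatment means only the carbon boost, so that photons fall inside the 12 weeks. At an assumed 2 Gy five times a week, 48 to 52 Gy takes 24 to 26 fractions, about 5 weeks, and 12 − 5 = 7.

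With Td = 12 months, a 12-week gap uses 11.2 of the 25 points. Only 1.25/1.112 − 1 = 12.4% growth from the start of radiotherapy is then needed. A 7-week gap uses 6.4 points.

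**4. Effect on the test.** Let f be the share of truly progression-free patients counted as progressed. The counted rate is 0.70(1 − f), and 37 × 0.70 × f patients are affected on average. No value of f can be derived from the article or from step 3, so these rows are illustrations.

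| f | Counted rate | Patients affected | Power, ≤ 13 events | Alpha, ≤ 13 events | Power, ≤ 12 events |
|---|---|---|---|---|---|
| 0 | 0.700 | 0 | 0.807 | 0.049 | 0.698 |
| 2% | 0.686 | 0.5 | 0.751 | 0.038 | 0.630 |
| 5% | 0.665 | 1.3 | 0.656 | 0.025 | 0.522 |

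**5. The two starting points.** The baseline window ends at the beginning of study treatment, while PFS starts on the first day of radiotherapy. Treatment Schedule lists only the carbon boost, and Inclusion criteria call the photon treatment prior. On that reading the initial assessment could even fall after photons have begun, hence after time zero if the first day of radiotherapy means the first photon fraction. The sections do not settle this.

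**The case against.** **Investigator judgement.** The dating rule applies only if later events show that progression was real, and clinical follow-up is to decide how a first increase is labelled. A lesion that rises 30% and then stays flat for 3 years is a course an investigator might well decline to call progression. This stands: miscounting is possible, not automatic. It does not remove the point, because the cautions named there are radiation reaction and surgical contrast uptake. Growth before treatment is neither, and case-by-case discussion is optional.

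**The planning images are the natural baseline.** Both sections mention CT and MRI, so the intention may be the same scans. But no sentence says so, and a smaller earlier measurement by the same technique would still be the reference as the rule is worded. An article may leave the imaging schedule to the full protocol; here, however, it states the window, reference and dating rule itself.

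**Twelve weeks is a ceiling.** This stands, and the 7-week figures reflect it.

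**Direction.** The computed bias lowers alpha as well as power, so it cannot create a false claim of efficacy. This stands for the mechanism computed. The opposite can also occur: an early scan enlarged by surgical enhancement raises the reference and may hide growth or suggest remission. The effect also disappears where the lesion later shrinks below its pre-treatment size.

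**Negative PFS times.** A reader might infer that back-dating to a planning scan, before time zero, damages the primary analysis. It does not. The confirmatory test is a binomial test of 3-year status, for which the exact event date within 3 years is irrelevant. Only the descriptive Kaplan-Meier analysis is touched.

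**Conclusion.** As written, the baseline window, the unrestricted smallest measurement and the PFS clock do not fit together, and growth of untreated residue can count towards a primary-endpoint event. This is a stated rule that can misclassify, not a detail left out.

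A reader might go further and infer that controlled tumours will be counted as failures and that the trial loses some 15 points of power. The article does not support that. Investigator judgement can prevent the miscount, no growth rate is given, and the 2% to 5% range is assumed and not linked to the doubling times. What can be said is that the test is sensitive: about 1.3 miscounted patients on average (f = 5%) would lower power from 0.807 to 0.656, or from 0.698 to 0.522 under the printed rule. The bias is mainly conservative. The change is worth making because the primary endpoint should not depend on scan timing and the correction is mostly wording.

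**What to change.** 1. In the section on assessing PFS by target lesions, name the last contrast-enhanced MRI before the first radiotherapy fraction as the reference scan. The MRI required under Treatment Planning can serve where it precedes photon treatment.
2. Under Radiological progression, restrict the smallest measurement to that scan and later ones.
3. State that no progression date may precede the first day of radiotherapy.
4. Reconcile study treatment (Treatment Schedule, Inclusion criteria, the baseline rule) with the first day of radiotherapy (the PFS section), so that the reference scan and the clock refer to the same start.

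**Cost.** Wording only, provided a planning MRI exists before the photons. The article does not say when that MRI is taken, so this has to be confirmed under item 4. Earlier postoperative scans are no longer used as a reference. Some interval between the planning scan and the first fraction remains, so the gap shrinks but does not vanish.

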### Radiological progression

The lesion must be measured in the two largest perpendicular diameters; the area should be defined as the product of these two diameters.

- Increase of the lesion on MRI or CT scans of more than 25% as measured by two perpendicular diameters compared to the smallest measurements ever recorded for the same lesion by the same technique.

- The appearance or new lesions with or without contrast enhancement.

### - Overall Survival -

Overall survival is the primary endpoint of the study. All patients will be followed until death. The duration of survival is the time interval between initial diagnosis (date of the neuropathology report) and the dated of death due to any cause. Patients not reported dead or lost to follow-up will be censored at the date of the last follow-up examination.

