**Methods/design:**

The Phase II-MARCIE-Study will evaluate a carbon ion boost applied to the macroscopic tumor in conjunction with photon radiotherapy in patients with atypical menigiomas after incomplete resection or biopsy.

Primary endpoint is progression-free survival, secondary endpoints are overall survival, safety and toxicity.

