### Study objectives and endpoints

The primary endpoint is progression-free survival at 3 years, therefore patients are followed within the trial protocol for a minimum 3 years after completion of study treatment. For the LPI (last patient in), the final study visit will be 3 years after study treatment to asses the primary endpoint. All other patients will be followed on a regular basis as stated below until death or until 3 years after LPI.

After RT, patients are scheduled for follow-up visits every 3 months or as needed clinically including contrast-enhanced MRI as well as thorough clinical-neurological assessment.

The last patient included into the study will be followed 3 years after treatment. This is considered the final study visit. All other patients will be followed regularly as described in detail until death or until 3 years after LPI.

The overall duration of the trial is expected to be approximately 72 months. Recruitment of the patients is planned over a time period of 36 months, minimum duration of the follow-up phase will be 36 months.

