### Analysis Variables

The primary outcome variable is progression-free survival rate at 3 years. Secondary objectives are the assessment of overall survival as well as 'toxicity' and 'safety'.

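### The Overall Survival section wrongly names overall survival as the primary endpoint, and it starts the survival clock before patients can be enrolled (a minor bias)

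*Protocol article*

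**What the plan says.** The protocol article uses the same sentence for two different endpoints:

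- Section Overall Survival: "Overall survival is the primary endpoint of the study".
- Section Progression-free Survival: "Progression-free survival is the primary endpoint of the study".

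The other sections that rank the endpoints agree with the second:

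- Abstract, Methods/design: "Primary endpoint is progression-free survival, secondary endpoints are overall survival, safety and toxicity".
- Methods and Design (opening text): PFS primary; overall survival, toxicity and safety secondary.
- Study objectives and endpoints: "The primary endpoint is progression-free survival at 3 years".
- Analysis Variables: "The primary outcome variable is progression-free survival rate at 3 years", with overall survival listed among the secondary objectives.
- Sample Size Calculation and Confirmatory Analysis: both are built on the 3-year PFS rate only.
- Descriptive Analysis: secondary endpoints are exploratory, and overall survival is reported by Kaplan-Meier curve, median and confidence interval.

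On time origins, the Overall Survival section measures the "time interval between initial diagnosis (date of the neuropathology report") and death from any cause. The PFS section starts on the first day of radiotherapy. The inclusion criteria require histological confirmation, list a prior photon course of 48-52 Gy, and require "beginning of study treatment no later than 12 weeks after surgery".

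On follow-up, the Overall Survival section has every patient followed to death. Study objectives and endpoints ends follow-up at death or at 3 years after the last patient in.

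**The concern.** A protocol has to name one primary endpoint without ambiguity. As published, the text could be cited in support of either PFS or OS when the results are reported.

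The OS clock is a separate and smaller matter. A patient who dies between the neuropathology report and enrolment never enters the trial. Everyone analysed has therefore survived that interval by construction (left truncation, or immortal time). An ordinary Kaplan-Meier estimate treats patients as at risk from the report date and so reads slightly too high. Death without progression is an event for both endpoints, yet the same death gets a longer duration for OS than for PFS. The abstract's Discussion says that outcome will be compared with standard photon treatment. In a single-arm trial that comparison is external, so the origin of the OS clock matters to it.

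**Working it through.** **1. Which endpoint was the trial designed on?**

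Inputs (Sample Size Calculation and Confirmatory Analysis): p0 = 0.50, p1 = 0.70 for the 3-year PFS rate, one-sided α = 5%, β = 20%, 37 evaluable patients, 40 recruited.

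Exact binomial test with n = 37, success declared at 24 or more progression-free patients (13 or fewer events):

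- α = P(X ≥ 24 | p = 0.5) = 0.0494, which matches the stated 0.049.
- Power = P(X ≥ 24 | p = 0.7) = 0.8071, so β = 1 − 0.8071 = 0.193.

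Among n = 28 to 44, 37 is the smallest n with α ≤ 0.05 and power ≥ 0.80. The stated sample size is therefore reproduced from the PFS inputs alone. (The article words its rejection rule as fewer than 13 events and prints the actual β as 0.0193. Those are separate matters and do not bear on which endpoint was sized.)

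For OS the article gives no null value, target, threshold, sample size or test. Calling OS secondary changes neither 37 nor 40, nor α, nor the confirmatory test.

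**2. How long can the pre-enrolment interval be?**

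The only limit given is 12 weeks from surgery to the start of study treatment. The neuropathology report comes after surgery, and enrolment comes no later than study treatment. The interval from report to enrolment is therefore shorter than 12 weeks. Its distribution is not given, so gaps of 4, 8 and 12 weeks are taken as a range, with 12 as a ceiling.

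**3. What is it worth?**

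Assumption: exponential OS with 75% alive at 5 years, counted from treatment start. The 75% is the rate that the Background quotes for the earlier carbon-boost series. The article does not give that series' time origin.

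- Hazard: λ = −ln(0.75)/5 = 0.0575 per year.
- With a gap g before entry, OS counted from the report reads exp(−λ(t − g)) instead of exp(−λt).

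| Gap g | Added to each OS time | 3-year OS (84.15% without gap) | 5-year OS (75.0% without gap) |
|---|---|---|---|
| 4 weeks | 0.9 months | 84.5% | 75.3% |
| 8 weeks | 1.8 months | 84.9% | 75.7% |
| 12 weeks | 2.8 months | 85.3% | 76.0% |

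For scale, the standard error of a 75% rate in 40 patients without censoring is √(0.75 × 0.25/40) = 0.068, or 6.8 points. The ceiling of 1.0 point is 1.0/6.8 = 0.15 of that, about one-seventh of a standard error.

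**4. Is the PFS origin a safe replacement?**

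Not necessarily. The inclusion criteria list the photon course as prior. If study treatment means the boost, the first day of radiotherapy can precede enrolment. Moving OS to the PFS origin would then shorten the guaranteed interval without removing it.

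**The case against.** The strongest reply is that the sentence is a drafting slip without consequence. All the working parts of the design (hypothesis, benchmark, sample size, test) concern 3-year PFS, and the Descriptive Analysis section settles that OS is exploratory. That stands as far as consequence goes: the intended reading can be recovered from the article itself. It does not remove the need to correct a plain misstatement of the primary endpoint.

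A reader might infer that two primary endpoints, each tested at one-sided 5%, allow up to 5% + 5% = 10% family-wise error. The documents do not support this. Only one test is specified, and OS has no null value or criterion that could be swapped in.

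A reader might also take 12 weeks as the amount of guaranteed survival. It is a ceiling on a different interval, surgery to study treatment, and the one that matters here is shorter. The objection that the resulting bias is small against sampling error also stands. Diagnosis is a clearly defined origin, and no joint OS and PFS display is planned, so the difference in origins is not an error in itself. What remains is that the planned estimator does not allow for late entry.

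On follow-up, it can be argued that survival tracking to death may continue outside the protocol period, since the PFS assessment text provides for imaging after the end of the study. That may be the intention, but the two sections do not say so.

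**Conclusion.** The point holds in two parts of unequal weight.

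- **Endpoint label.** The Overall Survival section contradicts the rest of the article. It is wrong as written and must be corrected. The design is unaffected: 37 evaluable and 40 recruited patients, α and the single test all stay.
- **OS clock.** OS starts before enrolment and carries guaranteed survival time. The direction always favours the treatment, but the size is minor: under 12 weeks per patient, and about 0.3 to 1.0 percentage points of 5-year OS for gaps of 4 to 12 weeks. This rests on exponential survival, on 75% at 5 years counted from treatment start, and on an assumed range of gaps. It affects a descriptive secondary endpoint only.

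The two statements on the length of follow-up also need reconciling, because they determine when OS observation ends.

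**What to change.** 1. In the Overall Survival section, state that overall survival is a secondary endpoint.
2. Count OS from enrolment, or from the start of study treatment provided that this is not before enrolment. If diagnosis, or a radiotherapy start before enrolment, is kept as the origin, estimate OS by delayed-entry (left-truncated) Kaplan-Meier, with each patient entering the risk set at enrolment.
3. Reconcile follow-up to death in the Overall Survival section with the limit of 3 years after the last patient in under Study objectives and endpoints. If survival is tracked beyond the protocol period, say so and give the cut-off date for the OS analysis.

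The cost is a few sentences. Reported OS times become slightly shorter (by 0.9 to 2.8 months for gaps of 4 to 12 weeks). Delayed-entry estimation, if chosen, needs the enrolment date recorded for each patient. Nothing in the sample size or the confirmatory analysis has to change.
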